### Strategies to improve adherence to interventions {11c}

Not applicable. Once performed, the trial interventions cannot be undone and crossover will not be possible.

### Relevant concomitant care permitted or prohibited during the trial {11d}

Not applicable. All trial patients will be treated according to standard of care.

### Provisions for post-trial care {30}

All trial patients will be treated according to standard of care. There is no anticipated harm that would differ from normal standard of care and no compensation for trial participation.

### Outcomes {12}

The primary endpoint of the study is PRWE at 1 year after the procedure. The secondary outcomes are Quick-Disabilities of Arm, Shoulder, and Hand (Q-DASH), pain on visual analog scale (VAS, 0 = no pain, 10 = worst imaginable pain), EQ-5D-5L, grip strength, wrist active ROM, global improvement, AEs, and radiologic evaluation (progress of arthritic changes, time to fusion in FCA participants) at the 1-year follow-up. Also, long term follow-ups (5 and 10 years) will be conducted.

The baseline data include patient age, gender, hand dominance, affected limb, duration of symptoms, smoking, education, type of work (desk-based to heavy manual), previous injuries, and surgery of the affected limb. Radiological baseline assessment includes wrist OA classification (SLAC/SNAC 0-IV), location of scaphoid non-union (distal, waist, proximal pole), ulnar variance, scapho-lunate- and scapho-capitate angle. Baseline clinical outcomes that will be assessed include ROM, and grip and key-pinch strength measurements.

The outcome variables and participant timeline are presented in Table 4.

**Table 4 Tab4:**
[figure not shown]
Schedule of enrolment, interventions, assessments, and data collection

*Primary endpoint

°Arthroscopy

*CBCT* Cone-beam computed tomography, *FCA* four-corner arthrodesis, *PRC* proximal row carpectomy, *PRWE* Patient-Rated Wrist Evaluation, *Q-DASH* Quick Disabilities of the Arm, Shoulder, and Hand, *RI* recruitment investigator, *ROM* range of motion, *SN* study nurse

### Primary outcome

#### Patient-Rated Wrist Evaluation

The Patient-Rated Wrist Evaluation (PRWE) is a patient-rated outcome measure for wrist and hand pathologies that is easy to administer and score in clinical practice. The PRWE is a 15-item questionnaire designed to measure pain and disability in activities of daily living [22]. The Finnish version has been translated, culturally adapted, and validated [23]. The score ranges from 0 to 100; a higher score indicates worse pain and function.

### Secondary outcomes

#### Quick Disabilities of the Arm, Shoulder, And Hand

The Quick-Disabilities of the Arm, Shoulder, and Hand (Q-DASH) is an upper extremity specific PROM with 11-items [24]. It is a widely used PROM for self-reported disability in various pathologies that affect the upper limb. Similar to the PRWE, the Finnish version has been translated, culturally adapted, and validated [25].

### Global improvement

Global improvement is a patient-centered standpoint of globally perceived benefit of the intervention. Global improvement is evaluated using five-step Likert scale from (− 2) “Much worse” to (+ 2) “Much better.”

### Pain

The visual analog scale (VAS) consists of a straight line with endpoints that define extreme limits to experiencing pain, from “no pain at all” and “worst possible pain” [26]. The subject is asked to mark their pain level on the line between the two endpoints. The distance (mm, 0 to 100) between “no pain at all” and the mark defines the subject’s pain. The VAS is a validated and reliable tool in pain assessment and is easy to use [27].

### Grip strength and wrist range of motion

Grip strength will be determined with a dynamometer (JAMAR hand dynamometer Model J00105, Lafayette, IN 47903, USA). Wrist active ROM will be measured using a manual goniometry following the American Society of Hand Therapists guidelines and Finnish Hand Therapy Societys guidelines [28, 29].

### Adverse events

Tendon, nerve, or arterial injury, chronic regional pain syndrome, infection, hematoma, deep vein thrombosis, non-union, implant-related complications, or any other conditions that can be attributed to the intervention will be regarded as an adverse event (event needing intervention or not resolving). Any complication leading to hospitalization, re-operation, or death will be considered as a major adverse event.

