## Abstract

**Background:**

Scapholunate advanced collapse (SLAC) and scaphoid non-union advanced collapse (SNAC) are common types of wrist osteoarthritis (OA). Non-operative treatment consists of pain medication, splinting, and avoiding activities that induce pain. However, in case a course of conservative treatment is unsuccessful, operative treatment is needed. The two most conventional operative approaches for SLAC/SNAC OA are four-corner arthrodesis (FCA) and proximal row carpectomy (PRC). Although FCA is the gold-standard operative technique and may lead to superior grip strength, the evident benefit of PRC is that it obviates any need for hardware removal and controlling for bony union. To date, no high-quality randomized controlled trial comparing FCA and PRC exists. As clinical outcomes seem comparable, a trial that assesses patient-reported outcomes, adverse events, and secondary operations may guide clinical decision making between these two procedures. Thus, the aim of this multi-institutional double-blind randomized controlled trial is to study whether PRC is non-inferior to FCA in treating SLAC/SNAC OA. We hypothesize that PRC is non-inferior to FCA with lower economic expanses.

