### Interim analyses {21b}

For ethical and safety reasons, an interim analysis will be performed after enrolment of 42 (50%) patients. The purpose of this analysis is to ensure that the rates of adverse events are within acceptable limits (within the normal rate of complications related to PRC/FCA). The interim analysis will be carried out blinded to the group allocation unless a clear deviation in the incidence of AEs is found, in which case the allocation will be unveiled, and the study discontinued.

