### Composition of the data monitoring committee, its role and reporting structure {21a}

The Helsinki university central hospital (HUCH) institute is responsible for (1) clinical onsite monitoring according to EN14155 and maintaining (2) a written “investigator file” and (3) a monitoring manual to ensure patient’s rights, patient’s security, and reliability of trial results. The trial sites will be visited onsite by a clinical research associate before study initiation. During the trial, sites will be monitored at regular intervals depending on the rate of recruiting and data quality using onsite visits and video meetings. A monitoring log is used to document all visits completed by the research associate from HUCH institute.

Moreover, a data safety and monitoring committee (DSMC) will be established. The DSMC consists of a clinician familiar with SLAC/SNAC treatment, a clinician familiar with clinical trials, and a statistician. The DSMC will evaluate the safety of the trial based on major adverse event reporting.

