### Adverse event reporting and harms {22}

AEs will be reported. Moreover, all major AEs will be documented and reported to the DSMC within 5 working days. All AEs occurring during trial participation will be treated according to standard of care.

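### The major adverse event definition omits lasting disability, so a non-resolving injury managed without admission or re-operation has no stated route to the DSMC

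*Protocol article*

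**What the plan says.** The Adverse events section (under Secondary outcomes) has two tiers.

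- **Ordinary tier.** It lists "Tendon, nerve, or arterial injury, chronic regional pain syndrome, infection, hematoma, deep vein thrombosis, non-union, implant-related complications", adds a catch-all for other conditions attributable to the procedure, and says these "will be regarded as an adverse event (event needing intervention or not resolving").
- **Major tier.** "Any complication leading to hospitalization, re-operation, or death will be considered as a major adverse event".

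Oversight is described in three further places.

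- Section {21a}: "The DSMC will evaluate the safety of the trial based on major adverse event reporting".
- Section {22}: "all major AEs will be documented and reported to the DSMC within 5 working days". For the rest, it says only "AEs will be reported".
- Section {21b}: "an interim analysis will be performed after enrolment of 42 (50%) patients". Its subject is adverse event rates in general, and a clear deviation would lead to unblinding and discontinuation of the study. It does not say which body performs or receives the analysis.

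Table 1 lists adverse events and major adverse events together as a secondary endpoint. The abstract justifies the trial by saying that "a trial that assesses patient-reported outcomes, adverse events, and secondary operations may guide clinical decision making between these two procedures", but Table 1 has no separate line for secondary operations.

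**The concern.** Whether an event counts as major depends on the care it leads to or on death, and not on how much lasting harm it does. In elective wrist surgery, permanent loss of hand function is a serious harm that may need neither a hospital bed nor a second operation. A site following the definition exactly would file it in the lower tier. The committee charged with judging safety is described as working from the upper tier.

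The DSMC could therefore be promptly told of a brief admission for a haematoma while no stated step tells it of a permanent nerve deficit. The stake is the committee's ability to notice an accumulation of lasting injuries while patients are still being randomized.

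**Working it through.** No arithmetic decides this point, and the protocol gives no figure to reproduce beyond the interim fraction, which agrees: 42 / 84 = 0.50. The check applies the stated rules to example events.

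**Step 1. Triggers for the major tier.** There are three: hospitalization, re-operation and death. None refers to permanence, disability or severity.

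**Step 2. Where non-resolution enters.** It appears only in the definition of an ordinary adverse event. The text names seven event types (counting tendon, nerve and arterial injury as one) plus the catch-all. None of the seven is major by its own severity. Each becomes major only through one of the three triggers.

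**Step 3. Apply the rules.**

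| Event | Course | Ordinary AE? | Major AE? | Stated route to the DSMC |
|---|---|---|---|---|
| Nerve injury, permanent | Outpatient care only | Yes, not resolving | No | None |
| Regional pain syndrome, unresolved | Outpatient care only | Yes, not resolving | No | None |
| Nerve injury | Leads to re-operation | Yes | Yes | Within 5 working days |
| Haematoma | Short admission | Yes | Yes | Within 5 working days |

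The first two rows are the gap. The third shows that it is conditional on how the event is managed.

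**Step 4. Does another provision close it?**

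- *Reporting of ordinary events ({22}).* No recipient or timing is given, so it neither sends these events to the DSMC nor rules that out.
- *Interim analysis ({21b}).* Its scope is wide enough to include these events, but the recipient is unnamed. It is also triggered by enrolment and not by follow-up, so for patients enrolled just before it, failure to resolve cannot yet be judged. No later aggregate review is described for the remaining 84 − 42 = 42 patients.
- *Individual safety concerns ({11b}).* These lead to unblinding and care of that patient. This is not a reporting route to the committee.

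None of the three supplies a stated DSMC route for the first two rows.

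**Step 5. Secondary operations.** Re-operation appears only as one trigger within the major tier, and the sentence is worded in terms of complications. Whether a further operation for persistent pain counts depends on whether it is classed as a complication of the procedure. No separate count is fixed.

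**The case against.** The strongest reply is that the sections agree with one another and that the article condenses a fuller protocol. The DSMC's inputs and listings may be set out in a charter that is not shown, and their absence here is no fault. That stands for the detail of what the committee receives. It does not cover the definition itself, which the article states in full and on which it expressly rests the committee's evaluation.

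The second reply is that lasting harm is not lost to the trial. This also stands. Unresolved events are recorded as adverse events, which are a secondary endpoint alongside major ones. Lasting loss of function would also show in PRWE at 1 year, in Q-DASH, pain, grip strength, range of motion and global improvement, and follow-up continues at 5 and 10 years. These are outcome analyses, though, and do not replace safety review during recruitment.

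A reader might be tempted by three stronger readings, none of which the document supports:

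- *Nerve, tendon or arterial injury or regional pain syndrome is never major.* Each is major if it leads to admission or re-operation.
- *Such events never reach the DSMC.* The text names no route but excludes none. The recipients of ordinary reports and of the interim review are simply unstated.
- *The trial could not give its re-operation rate by arm.* Re-operations that follow complications can be tabulated from the major-event records, the catch-all is broad, and healthcare use is collected for the cost analysis. What is missing is a fixed counting rule and a line of its own.

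**Conclusion.** The concern holds in a limited form. Events that do not resolve or that disable the limb, when managed without admission or re-operation, fall outside the major tier, and the protocol states no route by which the DSMC learns of them. This follows from a rule as written and would occur with perfect adherence to it.

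Its size cannot be given in events, because no complication rates appear in the document. With an unknown proportion p of patients affected, the expected number is 84 × p. The effect is on safety oversight. The primary analysis is not affected.

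The conclusion assumes that the full protocol uses the same definition and that no charter already gives the committee all adverse events. If a charter does so, the oversight gap closes and only the definition would merit revision. The point about secondary operations is minor and concerns presentation.

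**What to change.** 1. Extend the major adverse event definition with words such as: *or that results in persistent or significant disability of the limb*. Apply the existing five-working-day reporting to the DSMC.
2. State in {21b} that the interim adverse event review goes to the DSMC.
3. As a minor addition, report any re-operation on the index wrist, whatever its stated reason, by arm and separately from the major-event composite.

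The cost is one clause in the definition, one sentence in {21b}, one line in Table 1 and a few more expedited reports. The added recording should be small, because non-resolution and re-operation are already used to classify events, but the case report form is not shown and would need checking. Treatment, sample size and the primary analysis are unchanged.

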### Radiological evaluation

CBCT will be performed alongside the clinical follow-up at 6 and 12 weeks and 6 and 12 months. Moreover, standard PA and lateral view X-rays will be evaluated 5 and 10 years after study procedure. Time to union, non-union rates, implant-related complications, and development of postoperative OA will be recorded.

### EQ-5D-5L and cost-utility analysis

EQ-5D-5L is a standardized measure of health status developed by the EuroQol Group to provide a simple, generic measure of health for clinical and economic appraisal. Applicable to a wide range of health conditions and treatments, it provides a simple descriptive profile and a single index value for health status that can be used in the clinical and economic evaluation of health care. EQ-5D is designed for self-completion by respondents. It is cognitively undemanding and takes only a few minutes to complete [30]. In addition to health state evaluation, EQ-5D-5L will be used for the cost per quality-adjusted life year (QALY) gained evaluation after the procedure.

The costs will include treatment costs and possible costs of complications and sick leave. The costs of treatments and complications will be analyzed by collecting the actual use of healthcare services and multiplying the use of service by unit costs. Sick leaves and their societal costs will be collected from Social Insurance Institution of Finland (KELA).

### Participant timeline

Follow-up will take place at 3 and 6 weeks, at 3, 6, and 12 months, and at 5 and 10 years post-treatment. The trial schedule of enrollment, interventions, assessments, and data collection are presented in Table 4.

### Sample size {14}

The primary outcome measure is PRWE and the primary hypothesis of our trial is that PRC is non-inferior to FCA in the treatment of SLAC/SNAC OA I-II measured with PRWE total score. The non-inferiority margin is set at 11.5 points using the PRWE minimally clinically important difference [31]. To exclude the non-inferiority margin, the trial will require 37 patients in each group to observe MCID (non-inferiority margin 11.5, SD 14) in PRWE scores between the trial groups with a power of 90% and using a one-sided type I error rate of 2.5%. We will recruit 84 patients to account for 10% loss during follow-up.

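### The 37 patients per group are not reproduced from the printed inputs, which give 32 or 33 at a true difference of zero; the input that produced 37 should be stated

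*Protocol article*

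**What the plan says.** All of the sizing is in the protocol article under Sample size {14}. The hypothesis is non-inferiority: "the primary hypothesis of our trial is that PRC is non-inferior to FCA in the treatment of SLAC/SNAC OA I-II measured with PRWE total score". Next, it fixes the margin: "The non-inferiority margin is set at 11.5 points using the PRWE minimally clinically important difference". The result is that "the trial will require 37 patients in each group to observe MCID (non-inferiority margin 11.5, SD 14) in PRWE scores"; the calculation is made "with a power of 90% and using a one-sided type I error rate of 2.5" per cent. The allowance for loss follows: "We will recruit 84 patients to account for 10% loss during follow-up".

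Two other sections bear on the calculation. Sequence generation {16a} sets 1:1 allocation. Statistical methods for primary and secondary outcomes {20a} plans a mixed model for repeated measurements for continuous outcomes, and gives a one-sided 0.025 or two-sided 0.05 criterion. The article states no assumed true difference between PRC and FCA, no inflation factor other than the 10% loss, and no formula or software.

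**The concern.** The article prints a margin, an SD, a power and an error rate together with the number they are said to require. A reader who puts these four inputs into the usual non-inferiority formula does not get that number. The gap of 4 to 5 patients per group is too large for rounding or for the choice between the normal and t distributions.

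What is at stake is whether the design can be checked, not whether the trial is large enough. In a non-inferiority trial, readers judge the conclusion against the margin, the SD and the error rate. They need to know which values the trial was sized on. The number of evaluable patients needed also matters if recruitment or loss is reviewed later.

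**Working it through.** **Inputs.** From Sample size {14}: margin 11.5, SD 14, one-sided alpha 0.025, power 0.90, loss 10%. From Sequence generation {16a}: 1:1 allocation. Assumption, not in the article: true difference 0.

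**The plan's own step from 37 to 84.** 37 / 0.9 = 41.1, rounded up to 42 per group; 2 × 42 = 84. This reproduces.

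**The requirement per group, normal approximation.**
n = 2 × (z₀.₉₇₅ + z₀.₉₀)² × SD² / margin²
= 2 × (1.960 + 1.2816)² × 14² / 11.5²
= 31.1, so 32 per group.

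**The requirement per group, noncentral t.** With 2n − 2 degrees of freedom and noncentrality 11.5 / (14 × √(2/n)):

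| n per group | Power (t) | Power (normal) |
|---|---|---|
| 32 | 89.9% | 90.8% |
| 33 | 90.8% | 91.6% |
| 37 | 93.6% | 94.2% |
| 38 | 94.2% | 94.7% |
| 42 | 96.1% | 96.4% |

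The first n to reach 90% by t is 33. The printed 37 exceeds the requirement by 5 (5/32 = 16%) or 4 (4/33 = 12%).

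**Other conventional settings, rest unchanged.** One-sided 5% gives 26 (normal). Power of 80% gives 24 (normal) or 25 (t), and power of 95% gives 39 or 40. An equivalence test with one-sided 2.5% on each side gives 38.5, so 39. None gives 37.

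**What would give 37.**

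An input not printed, with every printed figure left intact:
- True difference against PRC: 0.8 points by t (11.5 − 10.69 = 0.81) or 0.95 by the normal formula (11.5 − 10.55).
- Inflation of 15%: 32 × 1.15 = 36.8, so 37. An allowance of this kind is sometimes made for a rank test, but the article names none.

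A printed figure that is not the one used:
- SD of 15.1 (t) or 15.3 (normal) in place of 14.
- Margin of 10.7 (t) or 10.6 (normal) in place of 11.5.
- One-sided alpha of 1.25%, as if 2.5% had been entered as a two-sided error: 36.8, so 37. This works only by the normal approximation; by t, 37 gives 89.1% and 39 are needed.
- Loss already included: 33 / 0.9 = 36.7, so 37. The step from 37 to 84 would then apply the 10% a second time.

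**Evaluable patients from 84.** 42 × 0.9 = 37.8, about 38 per group. With the printed inputs and a true difference of 0, power is about 94%.

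**The case against.** The strongest objection is that zero is the reviewer's assumption. A true difference of 0.8 to 0.95 points against PRC is a small, cautious allowance. It reaches 37 with every printed figure correct. A journal article may leave that value, the software or an inflation factor to the full protocol, which is not at hand. This stands. A reader might infer that the stated power or one of the stated inputs must be wrong, but the article does not support that, because an unprinted input explains the number equally well. It does not remove the point: the article prints inputs and a result that do not agree under the usual default, and nothing in it tells the reader what else was assumed.

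The second objection is that the discrepancy does no harm. Under the printed inputs the trial has more than 90% power, the step to 84 is sound, and neither the error rate nor the recruitment target changes. This also stands, and it limits the point to reporting.

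A reader might also take the phrase about observing the MCID as a sign that a superiority calculation was run. The article does not support this. The same sentence opens by naming exclusion of the margin as its aim, calls 11.5 the non-inferiority margin and uses a one-sided error. The phrase is clumsy and is only a matter of clarity.

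**Conclusion.** The point holds as a minor reporting correction. With margin 11.5, SD 14, one-sided 2.5%, 90% power and a true difference of 0 (assumed), the requirement is 32 per group (normal) or 33 (t), not 37. At 37 per group the power is 93.6% (t) to 94.2% (normal).

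An input is either unstated or misstated, and the article does not show which. In particular, it does not establish that the SD was really near 15, that the error rate was halved, or that the loss was counted twice. These are candidates only. Nor does the gap show that the trial is under-sized: under the printed inputs the discrepancy is conservative.

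**What to change.** Keep 84. In Sample size {14}, state the input that produced 37, including the assumed true difference between PRC and FCA, any inflation factor, and the formula or software.

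Only if the true difference was 0, and SD 14, margin 11.5 and one-sided 2.5% are confirmed as the values used, restate the result as follows: 33 per group gives 90% power; 84 randomised with 10% loss leaves about 38 per group and gives about 94%. This wording should not be adopted before that confirmation. If, for example, the SD used was near 15, the 94% would be wrong.

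For clarity, replace the phrase about observing the MCID with one that says the aim is to exclude a PRC minus FCA difference of 11.5 points or more on the PRWE, where higher scores are worse.

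The cost is the rewording of one paragraph. Recruitment and analysis do not change.
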